### Randomization

Before testing, eligible patients will be randomized and stratified for sex using the Robust Randomization App (RRApp, Version 3.0.1). A principal investigator, who is independent of the enrollment and data collection, will be responsible for the randomization process. He will store the randomization lists in sealed envelopes and hand them out to staff members immediately before the experimental sessions begin. Participants will be blinded and will not know the experimental condition to which they have been assigned. Staff members will be encouraged to maintain blinding as far as possible. The actual allocation will not be disclosed to the participants, and any code breaks must be promptly reported, along with the reason for the breach. Unblinding of participants will result in study discontinuation. To assess the effectiveness of the blinding procedures, as well as to gain insight into participant perceptions of their assigned interventions, participants will be asked whether they have any suspicions about which intervention group they have been assigned to upon completion of all laboratory sessions. As the analyst is also involved in the data collection process and therefore possesses knowledge of the participants’ group assignments, no double-blinding will be implemented for the data analysis. This potential for bias will be mitigated by adhering strictly to the pre-registered analysis plan [60], which outlines the statistical methods and criteria for evaluating outcomes.

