### Data preparation and statistical analysis

Data preparation and statistical analysis will be performed using IBM SPSS Statistics 26 (IBM Corp., Armonk, NY, USA). Following our pre-registered analysis plan [60], data will be screened for outliers using *z*-scores, and outliers which differ more than 3 standard deviations from the participants’ mean will be excluded from further analysis. In addition, participants will be excluded in case of elevated cortisol levels (e.g., > 12 nmol/L or *z* > 3.29) after arrival at the laboratory (i.e., at baseline) and after accommodating to the testing situation (i.e., at − 1 min relative to the TSST). Additionally, non-adherent participants whose missing values exceed 25% of the data will also be excluded from the analysis. In the next step, Kolmogorov–Smirnov tests will be conducted in order to check for normal distribution. If necessary, data will be log-, ln-, or inverse transformed to reduce skewness of biological data.

To analyze the data (i.e., to compare self-report measures as well as biological response and habituation indices between experimental groups), we will use separate analyses of covariance (ANCOVAs). Sex and BMI will be used as covariates in analyses of biological data, as these two variables have been repeatedly shown to be highly relevant for stress system activity [61, 62]. We will use the standard *p* < 0.05 criteria for determining if the ANCOVA and the post hoc test suggest that the results are significantly different from those expected if the null hypothesis were correct. The post-hoc Bonferroni test adjusts for multiple comparisons.

To investigate associations between primary psychological outcome measures and indices of biological stress measures, we will compute separate hierarchical linear regression models, regressing biological outcome measures onto psychological outcome variables. Again, sex and BMI will be included as covariates in these analyses. When examining state variables, the respective trait variable will be included as covariate in regression analyses.

We expect that certain psychological (e.g., emotion regulation, coping), demographic (e.g., age, gender, sex), and anthropometric (e.g., BMI) variables may be related to biological stress system activity. Therefore, we will test for relationships between these variables and primary outcome measures of biological stress responses in an exploratory fashion.

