### Data management plan

All data will be treated in compliance with the applicable German and European data protection regulations. All data will be pseudonymized, i.e., a random numeric code will be generated and used as data identifier. This code does not allow any conclusions to be drawn about the person. Personal data will be stored separately from all other data in computer files. These files will be protected by password and accessibility will be restricted to the principal investigators.

One year after the completion of the data analysis, all personal data will be deleted. In accordance with recommendations from the DFG, deidentified data will be stored on secure file servers for 10 years. Upon completion of the study, deidentified data will be made available to other researchers via public repositories. Only mean values and group statistics will be reported in publications.

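### The analyst knows the arms, and the printed data-preparation rules leave the cortisol cut-off and the transformation open: prepare and lock the data without the arm variable

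*Protocol article*

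**What the plan says.** The Randomization section of the protocol article is open about the arrangement. "As the analyst is also involved in the data collection process and therefore possesses knowledge of the participants’ group assignments", it concludes that "no double-blinding will be implemented for the data analysis". It calls this a potential for bias and names one mitigation: "This potential for bias will be mitigated by adhering strictly to the pre-registered analysis plan". The same section describes a principal investigator, independent of enrolment and data collection, who runs the randomisation and holds the lists.

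The section Data preparation and statistical analysis begins its data-preparation rules by invoking that pre-registered plan (reference 60). Some rules are firm: outliers beyond 3 standard deviations, exclusion above 25% missing values, ANCOVA with sex and BMI as covariates for biological data, and Bonferroni post hoc tests. Two are not:

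- Cortisol exclusion: "participants will be excluded in case of elevated cortisol levels (e.g., > 12 nmol/L or *z* > 3.29", applied to the arrival value and the value 1 minute before the stress test.
- Scale: after Kolmogorov–Smirnov tests of normality, "If necessary, data will be log-, ln-, or inverse transformed to reduce skewness of biological data".

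The Data management plan adds that "a random numeric code will be generated and used as data identifier". Saliva is assayed only after data collection is complete (Sample handling and laboratory analysis of biological samples), and no preliminary analyses are planned (Status and timeline of the study; Dissemination and analysis plans).

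**The concern.** A pre-registered plan offsets an unblinded analyst only where it leaves nothing to choose. The cortisol rule is introduced as an example and joins two criteria that can behave very differently: one is an absolute concentration, the other is relative to the sample. The text does not say whether both time points must be elevated or either one, nor which session counts. If the normality check fails, log and inverse are both allowed, with no order of preference.

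These choices settle who is analysed and on what scale habituation is measured, so they bear directly on Hypotheses 7 and 8. Made by someone who knows each participant's arm, they could tilt a borderline result, deliberately or not. The transformation sentence covers biological data in general, and Primary outcomes lists nine biological measures, so the opening is not confined to cortisol.

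**Working it through.** **The nearest printed figure.** The article gives no number for this point. Its sample size is the closest, and it sets the scale of the simulations. With f = 0.30, three groups and α = 0.05, the noncentrality is N·f² = 111 × 0.09 = 9.99 and power is 0.803, so N = 111 (37 per arm) reproduces. Read literally, the printed f² = 0.30 would give N = 36; that is a separate matter and does not affect this point.

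**Which choices are real.** Log and ln differ by a constant factor, so they give the same p-value. The effective scales are raw, log and inverse, and raw is ruled out when the normality check fails.

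**Simulation 1: size of the opening with free choice.** There is no arm effect, 40 per arm, and 3,000 trials per setting. Assumed inputs, not in the documents: lognormal cortisol, median pre-stress level 4, 6 or 8 nmol/L, log-SD parameter 0.5 (median 4) or 0.6 (medians 6 and 8).

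- Index: H = [t(peak₁) − t(pre₁)] − [t(peak₂) − t(pre₂)], with t(x) = x, ln x or −1/x.
- Test: F = [(RSS₀ − RSS₁)/2] / [RSS₁/(n − 5)], that is, two arm terms, an intercept and two covariates.
- Cut-off readings, on session 1 values: 12 nmol/L or z > 3.29, each at both or at either time point (four readings).
- Fixed comparator: 12 nmol/L at both time points, ln scale.

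Mean number excluded of 120:

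| Median (nmol/L) | 12, both | 12, either | z, both | z, either |
|---|---|---|---|---|
| 4 | 0.7 | 1.9 | 0.7 | 1.8 |
| 6 | 9.6 | 17.5 | 0.9 | 2.2 |
| 8 | 22.6 | 35.4 | 0.9 | 2.2 |

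Share of null trials with p < 0.05:

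| Median (nmol/L) | One fixed rule | Best of 4 cut-offs | Best of 3 scales | Best of all 12 |
|---|---|---|---|---|
| 4 | 5.5% | 6.1% | 11.8% | 13.1% |
| 6 | 5.3% | 7.2% | 12.2% | 17.6% |
| 8 | 5.4% | 9.1% | 12.0% | 20.3% |

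The Monte Carlo standard error at 5% is √(0.05 × 0.95/3000) = 0.4 percentage points, so the fixed rule is compatible with the nominal level.

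**Simulation 2: a narrower grid.** With 37 per arm, 4,000 runs, no covariates, and three cut-off readings on the session 1 arrival value only, one fixed rule gave 4.1%. The best of 3 cut-offs × 3 scales gave 10.8%.

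**Simulation 3: respecting the normality check.** With 37 per arm and the assumed range of Simulation 1 (median 4 to 8 nmol/L, log-SD 0.5 to 0.6), a Lilliefors-corrected Kolmogorov–Smirnov test chose raw or log, and only the three cut-off readings were free. The rate was 5.4% to 7.6%. The full 3 × 3 free choice under the same assumptions gave 10.8% to 15.0%. The rule as printed lies between these, because the sets of options are nested: it allows everything in the first (plus inverse when normality fails) and nothing beyond the second.

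**Would masked arm labels help?** The omnibus F statistic does not change when arms are renamed. An analyst holding arms A, B and C could pick the smallest p-value just as easily. Only a file with no arm variable removes that possibility.

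**The case against.** The strongest reply is that the pre-registered plan is a separate document, which the Randomization section describes as setting out the statistical methods and the criteria for evaluating outcomes. A journal article condenses, so the plan may name one cut-off and one transformation. That stands. A reader might infer that the safeguard fails and the result is unprotected; the documents do not support this, because the plan is not shown and the article itself fixes the test, the covariates, the 3 SD rule and the missing-data rule.

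Second, transformation is not free: the Kolmogorov–Smirnov check decides whether it happens, and that criterion does not depend on arm. This also stands, and it removes part of the inflation (Simulation 3). What remains is log versus inverse, and the cut-off.

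Third, if only session 1 values count, they precede the intervention, so arm cannot affect who exceeds a given cut-off. True, but the choice of cut-off could still be informed by arm.

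Fourth, departures could be noticed later by comparison with the pre-registered plan or from the public data. That is partly right, although the deposited data are described as pre-processed.

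Finally, the trial calls itself single-blinded and discloses the unblinded analysis with a reason. This is a declared trade-off, not a contradiction. None of these replies closes the printed gap or argues against masking the preparation step.

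**Conclusion.** The point holds in a limited form. The article accepts an analyst who knows the allocation and relies on strict adherence to a plan, yet the rules it prints while invoking that plan leave the cortisol cut-off, the time-point and session rule, and log versus inverse open. As printed, the safeguard does not fully cover these steps.

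The size is uncertain. Under assumed lognormal cortisol and no true effect, deliberate selection on one cortisol index gives anything from about 5% (5.4%, normality check respected) to about 20% (20.3%, all options free, median 8 nmol/L), against 4.1% to 5.5% for one fixed rule. A reader might take one of these figures as an upper bound or a forecast. It is neither: the rate moves with the assumed distribution and with the set of options, and unconscious steering would be expected to do less than deliberate selection. At a median of 4 nmol/L the two cut-offs exclude almost the same number of people; at 6 or 8 they differ greatly.

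This is best treated as a cheap improvement to the procedure, not as an error that undermines the trial.

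**What to change.** 1. After the assays are complete, the principal investigator who is independent of enrolment and data collection re-keys the final dataset with new random identifiers. The existing codes are not enough, since someone who collected the data may recognise them. Dates, written notes and the arm variable are removed entirely; masked labels do not suffice.
2. Post-intervention state rumination, state self-compassion and affect scores are held back until preparation of the biological data is locked, because Hypothesis 4 expects them to differ by arm and they could reveal it.
3. The analyst completes exclusions, ECG processing and transformations on that file and locks it with a date. Arms are then restored.
4. Data preparation and statistical analysis states one cortisol cut-off, one time-point and session rule, and one transformation rule, or confirms that the pre-registered plan does so. Randomization states that data preparation is blinded.

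The documents give no cost, so low cost is a judgement. It rests on what already exists: the independent role, the random codes, saliva assays run only after collection ends, and no earlier analyses. There is time to arrange it, since collection is planned to September 2026 and the trial's end is expected in September 2027. The price is a short delay and queries routed through the independent investigator. Masking will be imperfect because the analyst helped collect the data.

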### Data preparation and statistical analysis

Data preparation and statistical analysis will be performed using IBM SPSS Statistics 26 (IBM Corp., Armonk, NY, USA). Following our pre-registered analysis plan [60], data will be screened for outliers using *z*-scores, and outliers which differ more than 3 standard deviations from the participants’ mean will be excluded from further analysis. In addition, participants will be excluded in case of elevated cortisol levels (e.g., > 12 nmol/L or *z* > 3.29) after arrival at the laboratory (i.e., at baseline) and after accommodating to the testing situation (i.e., at − 1 min relative to the TSST). Additionally, non-adherent participants whose missing values exceed 25% of the data will also be excluded from the analysis. In the next step, Kolmogorov–Smirnov tests will be conducted in order to check for normal distribution. If necessary, data will be log-, ln-, or inverse transformed to reduce skewness of biological data.

To analyze the data (i.e., to compare self-report measures as well as biological response and habituation indices between experimental groups), we will use separate analyses of covariance (ANCOVAs). Sex and BMI will be used as covariates in analyses of biological data, as these two variables have been repeatedly shown to be highly relevant for stress system activity [61, 62]. We will use the standard *p* < 0.05 criteria for determining if the ANCOVA and the post hoc test suggest that the results are significantly different from those expected if the null hypothesis were correct. The post-hoc Bonferroni test adjusts for multiple comparisons.

To investigate associations between primary psychological outcome measures and indices of biological stress measures, we will compute separate hierarchical linear regression models, regressing biological outcome measures onto psychological outcome variables. Again, sex and BMI will be included as covariates in these analyses. When examining state variables, the respective trait variable will be included as covariate in regression analyses.

We expect that certain psychological (e.g., emotion regulation, coping), demographic (e.g., age, gender, sex), and anthropometric (e.g., BMI) variables may be related to biological stress system activity. Therefore, we will test for relationships between these variables and primary outcome measures of biological stress responses in an exploratory fashion.

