All participants will then be randomly assigned to one of two intervention programs (intervention group 1: rumination, intervention group 2: self-compassion) or to a control condition. Participants will then receive verbal and written instructions for the upcoming task and will be asked to either engage in coping behavior (rumination vs. self-compassion) or to think neutrally about a given topic (e.g., description of everyday life) and to write down their thoughts. To check whether the experimental manipulations were successful, psychological variables will be measured repeatedly before and after each experimental condition via questionnaires (see “Psychological assessments during the experiment”). Upon completion, participants will be dismissed and reminded of the follow-up appointment (+ 1 day) and the incentive they will receive via email. With this email, participants will receive instructions to reflect on the experienced stress situation, to review and complete their notes, and to bring these notes to session 2.

The following day, participants will be scheduled at approximately the same time for experimental session 2. Procedures will closely follow those of experimental session 1, with participants being instructed to review their notes from the previous session and engage in a slightly modified version of the mental arithmetic task during the TSST (i.e., serially subtracting 13 from 2011). In contrast to experimental session 1, no further intervention will take place on this day. At the end of this session, participants will be debriefed and dismissed. To ensure quality control of the experimental procedure, regular audits will take place at intervals of 6 to 8 weeks. These audits will be conducted by a principal investigator who is independent of the data collection process. The audits will include re-training sessions for the TSST panel, as well as for staff members who interact with participants. The objective of these audits is to reinforce adherence to the protocol, address any procedural deviations, and maintain a high standard of data integrity throughout the study.

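### The cortisol, outlier and missing-data exclusions are not confined to pre-intervention values, and the 3-SD screen precedes transformation, so they can remove data differently by arm

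*Protocol article*

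**What the plan says.** All three exclusion rules stand in the Protocol article, Data preparation and statistical analysis, which attributes them to a pre-registered plan.

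- **Outliers:** "outliers which differ more than 3 standard deviations from the participants’ mean will be excluded from further analysis".
- **Cortisol:** "participants will be excluded in case of elevated cortisol levels", at two time points: "after arrival at the laboratory (i.e., at baseline) and after accommodating to the testing situation" (-1 min relative to the stress test). The cut-off is introduced with e.g.: above 12 nmol/L, or z above 3.29. No session is named.
- **Missing data:** "non-adherent participants whose missing values exceed 25% of the data will also be excluded from the analysis".

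Only in the step after these screens does the section say that Kolmogorov-Smirnov "tests will be conducted in order to check for normal distribution", with transformation if needed to reduce skewness.

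Table 2 lists the arrival and -1 min saliva samples for each session. The Experimental setting and procedure section places the writing task after the first stress test, then an email asking participants to reflect and complete their notes. It has session 2 repeat session 1, with "participants being instructed to review their notes from the previous session". The Randomization section says the analyst knows the allocations ("As the analyst is also involved in the data collection process") and relies on strict adherence to the pre-registered plan to limit bias.

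**The concern.** A rule that removes people or values after allocation is harmless if it uses only what was measured before the intervention. It is not harmless if the intervention can change the value that triggers it, because the arms that remain are then no longer the arms that were randomised. The article's own rationale for the rumination arm is that rumination goes with sustained HPA-axis activation, so a session-2 cortisol rule could well act unevenly.

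The order of steps raises a second problem. Endocrine and inflammatory measures are expected to be right-skewed, which is why a transformation is planned. A z-score screen on the untransformed scale treats the ordinary long upper tail as error. Hypothesis 7 expects the strongest session-2 responses in the rumination arm and Hypothesis 8 the least habituation there, so that tail carries part of the effect the trial is looking for.

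Finally, a cut-off given as an example cannot be adhered to strictly, and adherence is the stated safeguard for an analyst who is not blinded.

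**Working it through.** The plan gives no expected number of exclusions, so there is no figure of its own to reproduce. The distributions below are assumptions, marked as such.

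**1. Timing.** The article describes randomisation both as before testing (Randomization) and as immediately after the first stress test (Abstract). On either description, session-2 samples follow allocation, the writing task and the emailed reflection. Session-1 arrival and -1 min samples precede the intervention.

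**2. Cortisol rule: who is removed.** Assume pre-stress cortisol is lognormal with median m of 4-6 nmol/L and log-SD 0.6, and that one high sample is enough. Then P(X > 12) = 1 - Φ(ln(12/m)/0.6).

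- m = 4, 5, 6: 3.4%, 7.2%, 12.4%.
- Level raised by an assumed 25% in the rumination arm (m = 5, 6.25, 7.5): 7.2%, 13.8%, 21.7%.

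If both samples must be high (assumed correlation 0.7), this falls to about 1-6% against 3-12%. With a lower median and spread (4 nmol/L, log-SD 0.5) and a shift of +0.2 log units for rumination and -0.2 for self-compassion, removal is 3.6% against 0.5%.

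**3. Cortisol rule: effect on the outcome.** The article defines response as peak minus the -1 min value, and habituation as response 1 minus response 2. The screened value is the one subtracted, so a high value lowers the response.

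- Assume median 4-6 nmol/L, log-SD 0.6, peak shift 0.30 and pre-level shift 0.21 log units, correlation 0.5-0.7, and peak 1.5-2 times the pre-level. The screened contrast is then 0.79 to 1.07 times the full one. If both samples must be high, it is 0.88 to 1.05.
- Under the second set of assumptions in step 2, it is 0.95 to 1.03.

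Applied to session 1 only, the rule caused no bias.

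**4. 3-SD screen: which mean.** If the mean is each person's own, the largest possible |z| among n values is (n - 1)/√n. This gives 6/√7 = 2.27 for seven saliva samples and 2/√3 = 1.15 for three blood samples. The rule could then never act within a session, so the workable reading is the mean across participants.

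**5. 3-SD screen: which tail.** For a lognormal with median 1 and log-SD s, mean = exp(s²/2) and SD = mean × √(exp(s²) - 1). With s = 0.6, the mean is 1.197, the SD 0.788 and the upper limit 1.197 + 3 × 0.788 = 3.56. Then ln(3.56)/0.6 = 2.12, so 1.7% lie above. The lower limit is negative, so no low value is ever flagged. For s from 0.4 to 0.8 the share is 1.3-1.9% per variable, or 1.6-2.2 of 120. A normal variable has 0.13% in its upper tail.

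**6. 3-SD screen: effect on the contrasts.** Simulation with 40 per arm, lognormal responses, log-SD 0.5-0.9, session correlation 0.6, and a rumination versus self-compassion difference of 0.67 or 0.81 log-SD. Those sizes are borrowed from the Power analysis section, where they describe intervention versus control. Responses in both sessions are screened.

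| Quantity | Raw-scale screen |
|---|---|
| Session-2 response contrast kept (Hypothesis 7) | 72-86% |
| Habituation contrast kept (Hypothesis 8) | 77-91% |
| Removed, rumination | about 4-6% |
| Removed, self-compassion | about 2-3% |

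The same screen on the log scale keeps 95-98% of the session-2 contrast. The percentages are for mean differences on the original scale. When the retained data are analysed on the log scale the loss is milder: power of the three-group test falls from 75-78% to 71-73% at 0.67, and from 90-91% to 87-88% at 0.81. With no true effect, the contrast is unbiased and the type I error stays near 5%.

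**7. Room in the sample size.** 120 - 111 = 9 spare participants, assigned in Power analysis to non-appearance and insufficient sample volume. The raw screen on one variable leaves about 115-117 of 120, so it alone would use 3 to 5 of the nine.

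**The case against.** The strongest reply is that the article does not say session-2 cortisol is used. That is right: no session is named, and if session 1 was meant the rule is sound. But the two samples exist in each session and nothing limits the rule, so session 2 is the plain reading until the text says otherwise.

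A reader might infer that the cortisol rule removes high responders and so shrinks the effect. The documents do not support that. The rule acts on the pre-stress level, and the outcome is a difference from that level, so the direction is open (step 3).

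A reader might also take the 3-SD rule to remove whole participants. The wording refers to outliers and may mean single values, although losing a peak or -1 min value still alters or deletes that person's index.

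The pre-registered plan is cited but not shown and may fix the cut-off and the session. The article should then state the same rule.

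Finally, "Unblinding of participants will result in study discontinuation" might be read as another analysis exclusion. It is a rule on conduct and does not say that data already collected are dropped.

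**Conclusion.** The point stands in a limited form. As written, the exclusions can act on values measured after the intervention, and the outlier screen acts on untransformed data. The hypothesis tests can be affected; the documents do not show that they will be.

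- **3-SD screen:** attenuation towards the null if Hypotheses 7 and 8 are true, to roughly 72-86% and 77-91% of the full contrasts on the original scale. There is no bias and no type I inflation if they are false. The lognormal form is an idealisation, since a delta score can be zero or negative.
- **Cortisol rule:** differential exclusion is possible on the plain reading, with an effect on the indices of either sign. The rates depend wholly on assumed levels and on an assumed intervention effect on next-day pre-stress cortisol, for which the article gives no figure.
- **Discretion:** the example cut-off, and the doubt whether one or both samples must be high, leave choices to an analyst who knows the arms.

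**What to change.** 1. Restrict the participant-level cortisol exclusion to the session-1 arrival and -1 min samples. Give one fixed cut-off and state whether one or both samples must exceed it.
2. Transform skewed biological variables before any z-score screening. State whether the screen removes single values or participants, and that the mean is taken across participants.
3. Make the analysis of all randomised participants with session-2 data primary, and report the present exclusion rules, including the 25% missing-data rule, as a sensitivity analysis.

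Relabelling the arms with codes would not mask the present analyst, who already knows who received what; fixed rules are the more reliable safeguard.

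The cost is a change of wording and one extra analysis run. Analysis is planned only after all data are collected, so there is time. The downside is that a few extreme but valid values stay in, with slightly larger variance.
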